## **8. CARDIOVASCULAR AND PULMONARY OUTCOMES**

The majority of the endpoints will be measured on the day before the exposure and at 4 and 22 hours after the exposure. Markers of inflammation in sputum will be measured only once because sputum will be induced only at 22 hours after the exposure.

**Health symptoms.** These will be assessed using a symptom questionnaire.

### **Endothelial and vascular function**

- Blood pressure.
- Brachial artery flow-mediated dilation (FMD) measured by ultrasound (BAU)

- ~~Brachial artery nitroglycerine (NTG)-mediated dilation measured by ultrasound (BAU-NTG)~~
- Brachial artery blood flow with Doppler probe immediately prior to the artery dilation measurements.

**Cardiac function.** Will be measured by electrocardiogram (24 hour Holter with 12-lead recording)

- Heart rate and HRV parameters in both the time domain (SDNN, PNN50, RMSSD) and the frequency domain (VLF, LF, HF, TP, LF/HF).
- Repolarization changes
- Arrhythmia
- ST-segment changes

**Blood markers.** The volume of venous blood to be collected will be a maximum of 150 ml over 3 days and no more than 500 mL over the study.

Endothelial function markers

- Microparticle production. Microparticle production by the vascular endothelium is a measure of endothelial cell activation and/or injury .
- Endothelin-1 and P-selectin. These molecules mediate various aspects of endothelial function.

Prothrombotic vascular state

- Von Willebrand factor (vWF) antigen- primary endpoint. vWF is a blood glycoprotein that plays a critical role critical in the initial stages of blood clotting. Its level in plasma (vWF antigen) will be measured in a commercial laboratory.
- Fibrinogen. It is a coagulation factor and an acute phase reactant and contributes to risk of cardiovascular outcomes.
- Tissue factor (TF) activity. Tissue factor is a potent pro-coagulant. The activity of TF associated with microparticles will be measured at UNC.
- Platelet activation. The activation of platelets is a critical component of atherothrombosis, and could be increased by air pollutants, including ozone.

Oxidative stress and systemic inflammation markers

- Several soluble markers will be measured [e.g., 8-isoprostane, nitrotyrosine, C-reactive protein (CRP), and interleukin-6 (IL-6)].
- Differential blood cell counts.

Lung injury markers

- Serum Clara Cell protein 16 (CC16). CC16 is a marker of the integrity of the air-blood barrier that is known to be affected by ozone.

**Markers of airway inflammation (in sputum samples)**

- Differential white cell counts. Total protein, IL-6, IL-8, TNF- $\alpha$ , CD40 ligand. These are well-documented markers of airway inflammation.

**Lung function (spirometry)**

- FVC, FEV1, FEV25/75. Spirometry will be performed on an ATS-approved spirometer using modified ATS performance criteria and NHANES III predicted values.

#### **Marker of genetic susceptibility to ozone**

- GSTM1 genotype in stored blood samples. *GSTM1* is a gene whose product, glutathione S-transferase, is an antioxidant enzyme that may be involved in susceptibility to ozone. The null polymorphism of this gene is very common in human populations but does not have any known clinical significance.

#### **9. SAMPLES or DATA TO BE ANALYZED IN A CORE LABORATORY**

- BAU-FMD and BAU-NTG (UCSF)
- Holter ECG (URMC)
- Blood markers: Endothelin-1 and P-selectin, vWF factor (level), fibrinogen, 8-isoprostane, nitrotyrosine, CRP, IL-6 (clinical lab)
- Blood markers: microparticle-associated TF activity (UNC) (vWF multimers may be also measured)
- Sputum markers of inflammation: Differential cell counts (each center); total protein, IL-6, IL-8, TNF- $\alpha$  (UNC)
- PES (Research Triangle Institute, RTP, NC)
- GSTM1 genotyping (clinical lab)

#### **10. TISSUE BANKING**

Blood and sputum samples will be banked for measurement of soluble markers of airway injury, inflammation and oxidative stress, and gene polymorphism for antioxidant enzymes.

#### **11. ASSESSMENT OF EXPOSURE PRIOR TO THE CHAMBER EXPOSURE**

Daily data on ambient air quality for ozone, PM2.5, and PM10 will be obtained from local monitoring sites.

The subject will wear a PES sensitive to ozone and nitrogen dioxide for 3 days prior to the pre-exposure day. The rationale is that it is possible that the health measurements will be influenced by both indoor and outdoor sources of pollution prior to the exposure sessions, including environmental tobacco smoke, occupational exposures, and/or other indoor PM sources that will not be captured with the ambient PM monitoring data. Possible indoor exposures (such as kerosene heaters) will be identified through the activity diary associated with the PES measurements.

#### **12. EXPOSURE GENERATION AND MONITORING SYSTEM**

The air entering the exposure chamber will be purified by passing it through several filters (Purafil, charcoal, HEPA ). Ozone will be generated by a high-voltage corona-spark, silent discharge ozonator. Temperature and relative humidity will be maintained at approximately 22 °C and 40%, respectively.

#### **13. DATA MANAGEMENT, ORGANIZATIONAL STRUCTURE, AND DATA SAFETY MONITORING PLAN**

A plan for data collection, transfer, and management will be developed in collaboration with the Data Coordinating and Analysis Center (DCAC) at the (New England Research Institute, Watertown, MA.)

The study will be overseen by the HEI Research Committee, a group of scientists with diverse expertise, which is responsible for developing and managing HEI research activities. Two special bodies of scientists will be set up to coordinate the conduct of the study, monitor the data collection, and discuss

issues related to subject safety and publication of the data: a Data Monitoring Board and a Steering Committee. The role of these two groups is summarized below.

The Data Monitoring Board (DMB) is composed of statisticians and cardiologists (including members of the HEI Research Committee and outside experts appointed by the Research Committee), the Data Coordinating and Analysis Center team, and HEI staff. The DMB will establish procedures for the timely submission of data from the centers, monitor the quality of the data, monitor the implementation of the data analysis plan, and monitor subject safety through review of data on adverse events. The DMB may also perform interim analyses of the data to assess whether early stopping of the study might be warranted. The DMB will report any significant findings directly to the HEI Research Committee and, as necessary, with the three clinical centers' investigators.

The Steering Committee is composed of the Principal Investigators of the four centers and members of the HEI staff and one member of the HEI Research Committee. The Steering Committee will implement the analytical plans, review reports to the individual institutional IRBs of adverse events and protocol violations, report adverse events and protocol violations to the DMB in a timely fashion, prepare and decide on authorship of reports and publications, and discuss and make decisions about requests for biological samples, data, and specific analyses (from either the individual centers' investigators or other researchers).

#### Data Safety Monitoring Plan

Adverse events will be graded according to the following scale:

Grade 1 Mild: transient mild discomfort; no limitation activity; no medical intervention or therapy required.

Grade 2 Moderate: mild to moderate limitation in activity, some assistance may be needed; **minimal noninvasive intervention or therapy (such as over-the-counter medication, application of ice, etc.) is allowed.** ~~no medical intervention or therapy required.~~

Grade 3 Severe: marked limitation in activity; some assistance required; medical intervention or therapy required, hospitalization possible.

Grade 4 Life-threatening: extreme limitation in activity, significant assistance required; significant medical intervention or therapy required; hospitalization probable.

Subjects will be encouraged to contact us if any adverse effects are noted after visits to the laboratories. They will have a 24-hour contact and pager numbers to report any potential adverse events that occur after study visits. If any subject has more than mild adverse effects from participation in the protocol or if several subjects have mild adverse effects, we will consider changing the protocol to improve subject safety and comfort. All adverse events that occur during the course of the study will be reported to the relevant IRB in accordance with current institutional guidelines. Subjects with two or more Grade 3 adverse events or with one Grade 4 adverse event will be withdrawn from the study. Information on adverse events will also be collected on a standardized data form and submitted to the Advance Data Entry and Protocol Tracking (ADEPT) system (at the Data Coordinating and Analysis Center) within 5 working days of occurrence (or as soon as the center is notified of the occurrence), with the exception of grade 3 and 4 events, which will be reported within 24 hour of occurrence (or as soon as the center is notified of the occurrence). The Data Coordinating and Analysis Center will periodically generate a report of all adverse events and submit it to the Steering Committee, the DMB, and HEI. As soon as the occurrence of a grade 3 or 4 event is reported to the ADEPT system, the Steering Committee and HEI will

be notified via email and the aggregated Adverse Events report will be generated and become available for viewing.

Frequency of Safety Reviews: Safety monitoring data, consisting of reports of adverse effects, as well as of study enrollment and dropout data, provided by the Data Coordinating and Analysis Center will be reviewed on the regular (at least monthly) Steering Committee teleconferences and reported to the DMB on a semi-annual basis.

Stopping Rules: We will stop the entire study (at all participating centers) in case of the following adverse events:

- 1) Death directly or indirectly due to any of the procedures performed in this protocol: e.g., exercise, medications administered, etc. (any Grade 4 adverse events).
- 2) Hospitalization directly or indirectly due to any of the procedures performed in this protocol: e.g., exercise, medications administered, etc. (any grade 4 adverse events).
- 3) Five subjects with Grade 3 events (described above).

The study will not be resumed until all the adverse event information has been discussed with the Steering Committee, the DMB, and the relevant IRBs and HEI have concurred with resumption of the study.

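### The Grade 4 bracket in stopping rules 1 and 2 does not match the sentences it follows or the adverse event grades, so three kinds of event have no single stop/continue answer

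*Protocol*

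**What the plan says.** All of this is in section 13 of the Protocol, mostly under Data Safety Monitoring Plan. It is current text, not the list of changes at the end.

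- **Grades.** The two upper grades both allow for hospitalization. The lower is "Grade 3 Severe: marked limitation in activity; some assistance required; medical intervention or therapy required, hospitalization possible". The higher, Grade 4 (life-threatening), is described by "significant medical intervention or therapy required; hospitalization probable". Grade 4 is the top of the scale, and there is no separate grade for death.
- **Scope of the stop.** "We will stop the entire study (at all participating centers) in case of the following adverse events".
- **Rule 1.** A death due directly or indirectly to a protocol procedure, followed by a bracket that refers to Grade 4 events of any kind.
- **Rule 2.** The trigger is "Hospitalization directly or indirectly due to any of the procedures performed in this protocol: e.g., exercise, medications administered, etc. (any grade 4 adverse events".
- **Rule 3.** "Five subjects with Grade 3 events (described above".
- **After a stop.** Resumption requires that the event information be discussed with the Steering Committee and the DMB, and that the IRBs and HEI agree.
- **Who is told, and when.** Centers report Grade 3 and 4 events to the ADEPT system within 24 hours. For the alert, the text begins "As soon as the occurrence of a grade 3 or 4 event is reported to the ADEPT system, the Steering Committee and HEI will" and continues with notice by e-mail. Safety, enrollment and dropout data are reviewed by the Steering Committee at least monthly and "reported to the DMB on a semi-annual basis". Earlier in section 13, the Steering Committee is also required to pass adverse events to the DMB in a timely way, and HEI staff and the coordinating center team are listed as DMB members.

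**The concern.** In rules 1 and 2 the sentence and the bracket describe different sets of events. The sentence turns on outcome (death, hospitalization) and on relation to a protocol procedure. The bracket turns on grade alone and drops the relatedness condition. The two would coincide only if every related hospitalization were Grade 4, and if every Grade 4 event were both related and either fatal or hospitalized. The scale says neither.

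The protocol does not say whether the bracket restricts the sentence, adds to it or replaces it. If it replaces the sentence, rules 1 and 2 become the same rule.

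This is a study-wide safety rule for volunteers aged 55 to 70 who exercise during ozone exposure. The error can go either way: exposures continue although a written rule says stop, or all three centers halt for an event the rule was not meant to cover. The DMB discussion required before resumption applies only once the study has stopped, so an event read as non-stopping does not reach the DMB by that route.

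**Working it through.** No sample size, power or error rate enters, and the plan gives no figure to reproduce. The check is a logic table.

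**Inputs.** The Grade 3 and Grade 4 definitions and rules 1 to 3, all from the Data Safety Monitoring Plan.

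**Event classes.** Grade (3 or 4), hospitalized or not, fatal or not, procedure-related or not: 2 × 2 × 2 × 2 = 16. A fatal Grade 3 event is excluded, because rule 1 places death with Grade 4. That removes 4 and leaves 12.

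**Readings of the bracket in rules 1 and 2.**
- A: ignored. Stop if (death or hospitalization) and related.
- B: restricts. Stop if A holds and the event is Grade 4.
- C: adds. Stop if A holds or the event is Grade 4.
- D: defines. Stop if the event is Grade 4.

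| Event (single subject) | Classes | A | B | C | D |
|---|---|---|---|---|---|
| Grade 3, not hospitalized, related or unrelated | 2 | no | no | no | no |
| Grade 3, hospitalized, unrelated | 1 | no | no | no | no |
| Grade 3, hospitalized, related | 1 | stop | no | stop | no |
| Grade 4, neither hospitalized nor fatal, related or unrelated | 2 | no | no | stop | stop |
| Grade 4, hospitalized and/or fatal, unrelated | 3 | no | no | stop | stop |
| Grade 4, hospitalized and/or fatal, related | 3 | stop | stop | stop | stop |

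**Result.** Undetermined: 1 + 2 + 3 = 6 of 12. Same answer on every reading: 2 + 1 + 3 = 6 of 12.

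**Grade 3 hospitalization, number of subjects needed to stop.** Under A or C, one related case is enough (rule 2). Under B or D, rule 2 does not apply to Grade 3, and the case counts only toward the five subjects of rule 3. The contrast is 1 against 5.

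**Related provision.** The rule that withdraws an individual subject (two or more Grade 3 events, or one Grade 4 event) works at a different level and contradicts none of the above.

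**The case against.** The strongest reply is that the three rules are a list of alternatives. Rule 3 does not say that Grade 3 events stop the study only at five subjects. Read this way, a procedure-related hospitalization stops the study at any grade under rule 2, rule 3 adds a trigger for accumulating Grade 3 events, and the two do not conflict. This is right as far as it goes: rules 2 and 3 are compatible on their own, and the figure of five arises only if the bracket restricts or defines rule 2. But it settles only the Grade 3 case, and only by assuming that the bracket does not limit the rule. Whether an unrelated Grade 4 event, or one with neither hospitalization nor death, stops the study remains open.

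Several stronger inferences are tempting, and the documents do not support them.

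- *The rules fail for the gravest events.* They do not. A procedure-related Grade 4 hospitalization or death stops the study on all four readings. The lack of a grade for death does not weaken rule 1 for related deaths, since it names death outright.
- *Each center would decide for itself.* The stop covers all centers, and Grade 3 and 4 events go through one system to one Steering Committee that includes the centers' principal investigators. The text describes shared handling.
- *The DMB might not hear of an event for six months.* The semi-annual interval is not its only source. The Steering Committee must report adverse events to it in a timely way, the coordinating center sends it periodic adverse event reports, and HEI staff and the coordinating center team belong to it. What remains is narrower: the DMB as a body, including its outside experts, is not named in the immediate alert, and the timely reporting has no stated limit.

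**Conclusion.** The point holds as an internal contradiction between the stopping rules and the adverse event grades. Three kinds of event have no single answer:

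(a) a procedure-related Grade 3 hospitalization;
(b) a Grade 4 event not related to study procedures;
(c) a Grade 4 event with neither hospitalization nor death.

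Categories (b) and (c) overlap in one class, so together the three cover 1 + 4 + 2 − 1 = 6 of the 12 classes. This counts types of event and is not a probability. The documents give no expected rates for Grade 3 or 4 events, so how often the ambiguity would arise cannot be estimated.

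The count rests on two assumptions: that a fatal event is Grade 4, and that the four readings cover the plausible meanings of the bracket.

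The alert list is a secondary point. It is a gap in routing that sits poorly with the DMB's duty to monitor safety. It is not a contradiction, and no particular delay can be claimed from it.

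**What to change.** Reconcile the Stopping Rules with the grade definitions. For rules 1 and 2, state whether the bracket restricts, adds to or defines the rule, and whether relation to a protocol procedure is required. A short table listing death, hospitalization at each grade, and Grade 4 events with and without hospitalization, each split into related and unrelated, with one action per row, would remove the ambiguity. Which action belongs in each row is for the sponsor, the investigators and the DMB to decide.

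Separately, square the Grade 3/4 alert list with the DMB's safety role, either by naming the DMB as a recipient of the existing e-mail or by giving the Steering Committee's report to it a stated time limit.

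The cost is a wording amendment to section 13 and, if chosen, one more recipient group. Sample size, measurements and analysis are unaffected.

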#### 14. RANDOMIZATION AND DATA ANALYSIS

There are six possible ways of ordering the receipt of three different levels of ozone. Each ordering defines an exposure plan. Participants will be randomly assigned to one of the six plans using permuted blocks with institutional balancing. This ensures that that within each center approximately the same number of subjects would receive each exposure plan. For randomization by permuted blocks, the participants are randomized in blocks of six so that within each block of six participants all exposure plans are used. The assignment of the exposure plans within a block of six participants is randomly determined.

The primary analysis for this multi-center crossover design is a mixed effects linear model. For each of the three exposures (no ozone, 70 ppb, 120 ppb), most outcome variables will be measured pre-exposure, 4 hours after exposure, and 22 hours after exposure. The 4 hr and 22 hr measures will be the dependent variables with the baseline measure as a covariate. That will allow us to assess the effect of ozone on change from baseline to the two post-exposure measures. We will assume an autoregressive correlation structure among the repeated factors. If ozone exposure does affect how much the outcome variable changes from pre-exposure to one or both post-exposure times, we would expect to find an interaction effect of time by ozone level to be statistically significant.

The linear model for this design is:

$$y_{i:jk(l)t} = \mu + y_{i:jk(l)0} + \tau_k + \gamma_{(l)} + \alpha_j + \beta_{i:j} + \theta_t + \tau\theta_{kt} + \varepsilon_{i:jk(l)t},$$

where  $y_{i:jk(l)t}$  is the outcome measure for subject  $i$  in center  $j$  at ozone exposure  $k$  preceded by exposure  $l$  at time  $t$ . Specifically,  $y_{i:jk(l)0}$  is the outcome pre-exposure level of the outcome measure ( $t=0$ ).  $\tau_k$  is the direct effect of treatment  $k$  and  $\gamma_{(l)}$  is the residual or carry-over effect of treatment  $l$ .  $\alpha_j$  is the effect of center  $j$  and  $\beta_{i:j}$  is the effect of subject  $i$  in center  $j$ ,  $\theta_t$  is the effect of time  $t$  and  $\tau\theta_{kt}$  is the interaction effect of treatment  $k$  at time  $t$ .

If the outcome measure is Gaussian, the model will be estimated by a least squares linear model. If the outcome measure is continuous but not normally distributed, we may consider a normalizing transformation. If the outcome measure is dichotomous we will use a general linear model with binary errors and a logit link function. Using this basic model we can include additional terms including stratification or other effects (e.g. gender) and interaction effects for treatment with stratification factors or center. If the “wash-out” period is sufficiently long we may omit the residual effect from the model, although there is little or no loss in efficiency in including it even if it is 0.

The primary outcome analysis will be conducted on the 90 participants who complete all three exposure sessions. In order to achieve 90 participants with complete data, we will recruit approximately 140 (64% completion rate) men and women. Due to randomization, this attrition will not affect the internal validity of the study but it may affect the generalizability of the results. We will compare the characteristics of those who complete the protocol compared to those who do not using logistic regression analysis. Factors to be examined include baseline characteristics of the participants including age, gender and selected measures of cardiovascular health as well as ozone exposure at the initial session and study center.

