## **2. HYPOTHESES**

### **Primary hypotheses**

We hypothesize that ozone reaction products in airways surface liquid interact with lung cells (e.g., epithelial cells, macrophages, nociceptive sensory nerve endings, endothelial cells), and that these cells produce mediators that enter the pulmonary and systemic vasculature. In addition to its (local) effects on airway inflammation and lung function, ozone may have the following cardiovascular effects:

- (1) altered autonomic balance (measured as changes in heart rate and heart rate variability (HRV)), cardiac arrhythmia, and repolarization
- (2) altered systemic vascular function [measured as brachial artery flow-mediated dilation (FMD) ~~without and with nitroglycerin (NTG)~~ – primary endpoint].
- (3) pro-thrombotic vascular state (measured as increase in von Willebrand factor antigen in blood – primary endpoint). Secondary endpoints are: increase in microparticle-associated Tissues Factor activity and platelet activation.

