## 6. EXPOSURE VISITS AND TIMELINE OF MEASUREMENTS

Subjects will be exposed to clean air, 70 ppb (low), and 120 ppb (high) ozone for 3 hours in a randomized order. Each exposure session involves 3 consecutive days as shown below. There will be a minimum 2-week period between the exposure sessions.

| Exposure (order will be randomized) | Pre-exposure day | Exposure day | Post-exposure day |
|-------------------------------------|------------------|--------------|-------------------|
| Clean Air                           | Visit 3          | Visit 4      | Visit 5           |
| 70 ppb ozone                        | Visit 6          | Visit 7      | Visit 8           |

|               |         |          |          |
|---------------|---------|----------|----------|
| 120 ppb ozone | Visit 9 | Visit 10 | Visit 11 |
|---------------|---------|----------|----------|

**Prior to visit 3, 6, and 9** the subjects will receive reminder phone calls and will be asked to answer the *Before Pre-exposure Visit Phone Questionnaire*, which includes questions about the subject's health and medication use and gives a few reminders about the upcoming visit or, if necessary, provides the opportunity to reschedule the visit.

**Visit 3, 6, and 9 - pre-exposure day.** The subject will arrive at the laboratory or CRC at 11:30 am –12:00 noon. A low-fat lunch (25-30% fat) will be provided. The *Ozone Monitor Activity Diary* and PES will be collected and the subject will answer *Pre-Exposure Day Health Questionnaire*. In a woman who has not yet completed menopause, a urine pregnancy test will be done.

The following procedures will be carried out: measurement of vital signs, venous blood draw (up to 30 mL), ultrasound measurement of flow-mediated (FMD) and ~~nitroglycerin-mediated (NTG)~~ brachial artery dilation ultrasound (BAU). A box dinner will be provided. The subject will spend the night at the CRC or at a nearby hotel. Before discharge the subjects will be reminded that the researchers believe it is important to avoid any environmental exposure that might possibly affect his/her reaction to the controlled exposure scheduled for the following morning. For that reason they are providing a boxed supper and close-by sleeping accommodation in a nonsmoking environment. They will stress that the subject's thoughtfulness and cooperation is very much appreciated.

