**Visit 4, 7, and 10 – exposure day.** The subject will arrive at the laboratory or CRC at 7:00 – 7:30 am. A regular breakfast will be provided. The following events will occur: blood pressure (and other vital signs) will be measured; the subject will complete the symptom questionnaire; the subject will wear a Holter monitor, heart rate variability (HRV) will be measured (the subject lies quietly for 5 minutes then the ECG is recorded for 5 minutes under tidal breathing) and continuous ECG recording will begin; spirometry will be measured.

The exposure will start between 8:00 and 8:30 am and will last 3 hours. The subject will alternate a 15-minute exercise period with a 15-minute rest period. Subjects will be blinded to ozone dose and order of exposure. Assignment of each subject to the exposures will be randomized (see Section #15).

Minute ventilation will be measured with pneumotachograph between 8 and 10 minutes of the first exercise period and during the last 2 minutes of the first, second, fourth, and sixth exercise period and the exercise load adjusted as needed. Blood pressure will be measured during a rest period, 5 minutes before the first, third and fifth exercise period. Heart rate will be measured twice during the first exercise period and once during each of the other exercise periods.

The symptom questionnaire will be filled out by the subject in the chamber during the last 15 minutes of exposure. Immediately after exposure blood pressure (and other vital signs) will be measured, then HRV and spirometry. A low-fat (25-30% fat) lunch will be provided.

Approximately 3.5 hours after the end of the exposure the sequence of the measurement will be: HRV, venous blood draw (up to 30 mL), BAU FMD and ~~NTG-mediated dilation~~, symptom questionnaire, and blood pressure (and vital signs). The subject will be sent home wearing the Holter monitor. The subject will leave the laboratory or CRC at around 4:00 pm.

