**Visit 5, 8, and 11 –post-exposure day.** The subject will arrive at the laboratory or CRC at 8:00 am. The subject will need to be fasting from 7:30 am 2 hours prior to sputum induction, in order to avoid contamination of the sputum specimen. The sequence of measurements will be: vital signs, symptom questionnaire, HRV, venous blood draw (up to 30 mL), and spirometry/sputum. Blood pressure may be measured. The subject will leave the laboratory and CRC at around 10:30 am and will be given the *Ozone Monitor Activity Diary* and PES (and associated instructions) to wear before the next exposure visit (with exception of visit 11).

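### Section 14 looks for an ozone effect in the time-by-ozone interaction, which only compares 4 h with 22 h and cannot be estimated for FMD

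*Protocol*

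**What the plan says.** Section 14 of the protocol specifies a mixed linear model for the crossover. "The 4 hr and 22 hr measures will be the dependent variables with the baseline measure as a covariate". The model equation agrees: the pre-exposure value stands on the right-hand side. The remaining terms include exposure (τ_k), time (θ_t) and their interaction (τθ_kt); τ_k "is the direct effect of treatment" k.

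The section then says how an ozone effect would show itself. If ozone alters "how much the outcome variable changes from pre-exposure to one or both post-exposure times", then "we would expect to find an interaction effect of time by ozone level to be statistically significant". It names no other test or contrast for an ozone effect.

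Section 2 marks two endpoints as primary. One is von Willebrand factor (vWF) antigen. The other is systemic vascular function, "measured as brachial artery flow-mediated dilation (FMD").

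Section 6 gives the schedule:
- The pre-exposure day includes "ultrasound measurement of flow-mediated (FMD) and" a second, struck-out dilation measurement.
- On the exposure day, about 3.5 h after exposure ends, "the sequence of the measurement will be: HRV, venous blood draw (up to 30 mL), BAU FMD".
- On the post-exposure day, "The sequence of measurements will be: vital signs, symptom questionnaire, HRV, venous blood draw (up to 30 mL), and spirometry/sputum". FMD is not listed.

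Blood is drawn on all three days, so vWF can have both a 4 h and a 22 h value. FMD has only the value at about 4 h.

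**The concern.** The sentence about the interaction belongs to a different model, one in which the pre-exposure value is itself a level of time. There, a change from baseline that depends on ozone is a time-by-ozone interaction. Once baseline becomes a covariate, the ozone effect on the post-exposure values lies in τ_k together with τθ_kt. The interaction alone carries only the difference in effect between 4 h and 22 h.

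The error runs in one direction. A real interaction implies an ozone effect at one time at least, so a significant result would still be informative. A non-significant result says little, because a sustained effect of equal size at both times leaves the interaction null. The study asks whether near-ambient ozone has any acute cardiovascular effect, so a criterion that is insensitive to a sustained effect could lead a reader to a false negative.

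For FMD the named criterion cannot be computed at all.

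**Working it through.** **Figures in the plan.** Section 14 analyses 90 completers (3 centers × 30) and recruits about 140 at 64% completion. 90/140 = 64.3% and 90/0.64 = 140.6, so this reproduces. The protocol gives no alpha, power, effect size or SD, and no value for the autoregressive correlation.

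**What the interaction tests.** Let e_k4 and e_k22 be the effects of exposure k against clean air at 4 h and 22 h. The interaction hypothesis is e_k4 − e_k22 = 0 for both ozone levels. If e_k4 = e_k22, it is true whatever the size of the effect, so the rejection rate is alpha. This needs no assumption about effect size or correlation.

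**Assumptions for the power figures (not from the protocol).** Two-sided alpha 5%; residual SD 1 at each time; no carry-over; effect at 4 h of 0.5 SD at 120 ppb and, by linearity, 0.5 × 70/120 = 0.292 SD at 70 ppb; 22 h effect equal to r times the 4 h effect; correlation ρ between the two residuals within a session.

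**Formulas.** The mean of 0, 0.292 and 0.5 is 0.264. The sum of squared deviations is 0.0696 + 0.0008 + 0.0557 = 0.1262, and 90 × 0.1262 = 11.35. The noncentrality parameters are:
- interaction (2 and 178 df): 11.35 (1 − r)² / [2(1 − ρ)]
- exposure effect averaged over times (2 and 178 df): 11.35 (1 + r)² / [2(1 + ρ)]
- exposure effect at 4 h alone (2 and 178 df): 11.35
- joint test of τ_k and τθ_kt (4 and 356 df): the sum of the first two

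Example with ρ = 0.5 and r = 1: interaction 0, average 11.35 × 4/3 = 15.14. With r = 0.5: interaction 11.35 × 0.25/1 = 2.84, average 11.35 × 2.25/3 = 8.52.

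**Power from the noncentral F distribution:**

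| 22 h effect | ρ | Interaction | Time-averaged | Joint, 4 df |
|---|---|---|---|---|
| equal to 4 h | 0 | 5% | 99% | 98% |
| equal to 4 h | 0.3 | 5% | 97% | 93% |
| equal to 4 h | 0.5 | 5% | 94% | 89% |
| equal to 4 h | 0.6 | 5% | 93% | 87% |
| half of 4 h | 0 | 17% | 90% | 87% |
| half of 4 h | 0.5 | 30% | 74% | 77% |
| half of 4 h | 0.6 | 37% | 71% | 78% |
| none (4 h only) | 0 | 55% | 55% | 77% |
| none (4 h only) | 0.3 | 72% | 44% | 81% |
| none (4 h only) | 0.6 | 93% | 37% | 94% |

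The comparison at 4 h alone has 86% power throughout. Setting the 70 ppb effect to 0.25 SD instead of 0.292 moves every entry by less than one percentage point. A simulation of 4,000 trials with 0.25 and 0.5 SD and equal effects at both times rejected the interaction in 5.0% (ρ = 0.3) and 5.4% (ρ = 0.6), and the time-averaged effect in 96.8% and 92.5%.

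**FMD.** The fixed effects for mean, exposure (2), time (1) and interaction (2) make six columns. With 4 h and 22 h data the rank is 6. With 4 h data only it is 3: the mean and the two exposure terms. θ_t and τθ_kt are therefore not estimable for FMD, but τ_k is.

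**The case against.** The best defence is that section 14 sets no decision rule. The sentence states an expectation, the mixed model as a whole is called the primary analysis, and τ_k is in it. A reader might infer that a persistent ozone effect would have to be declared absent. The text does not go that far: nowhere does it say that ozone will be judged inactive unless the interaction is significant. What remains is that the expectation is wrong for the model as written, that it expressly covers effects at both times, and that no other criterion is offered.

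A reader might also infer that the interaction is blind to any effect present at both times. That is exact only for equal effects. With a 22 h effect half the size of the 4 h effect it is a loss of power, and a 4 h-only effect can be detected well.

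On FMD, a reader might infer that the primary endpoint cannot be analysed. The documents do not support this. Sections 8 and 14 apply the three-time schedule to most outcomes, not all, section 14 allows the basic model to be extended, and dropping the time terms leaves a model that can be fitted. A separate analysis plan, which is not at hand, may write that model out. It is still true that the criterion stated in the protocol does not exist for FMD.

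Finally, apart from the 5% result, the power figures depend on assumed values.

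**Conclusion.** The concern holds in limited form. The sentence in section 14 misdescribes what the interaction tests in the protocol's own model. For an equal effect at 4 h and 22 h, interaction power is alpha, without further assumption. Under the assumptions listed, the joint test then has 87-98% power and the time-averaged test 93-99% over correlations 0 to 0.6. For a 22 h effect half the 4 h effect, interaction power is about 17-37%. For a 4 h-only effect it is about 55-93%, so clearly unequal effects remain detectable.

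For FMD, one of the two endpoints marked primary, the interaction is undefined, while the exposure effect is estimable. The model already contains the terms needed. The fault lies in the stated criterion, not in the design or the data.

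**What to change.** Replace the sentence in section 14 so that the ozone effect is judged by the exposure terms:
- For outcomes with both post-exposure times, such as vWF antigen, use the joint test of τ_k and τθ_kt, or the contrasts of 70 and 120 ppb against clean air.
- For FMD, test τ_k on the 4 h value in a model without θ_t and τθ_kt.
- Use the interaction only to describe whether the effect changes between 4 h and 22 h.

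A 0-70-120 trend contrast is optional and does not follow from the defect.

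The cost is wording in section 14, with any analysis plan kept consistent; no new data or visits are needed. The joint 4-df test gives up some power against the time-averaged test when the effect is constant (for example 89% against 94% at correlation 0.5). In return, it holds up much better when the effect is confined to 4 h (77-94% against 37-55% over correlations 0 to 0.6).
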